### Statistical analysis

A sample size calculation was conducted to determine the number of medical records needed in each of the 14 study hospitals, to achieve an 80% power at an alpha level of 0.05 to address the quantitative aims of the study while taking the clustered randomization into consideration [61, 62]. Sample size calculations were based on an intracluster correlation of 0.03. In case intracluster correlation is lower than 0.03, our statistical tests provide an even larger statistical power. For the between-group comparisons regarding the binary outcomes of Aim 1, detecting an absolute difference in a proportion between the two groups of 16% with an at least 80% power, using a Z-statistic that accounts for the intracluster correlation, requires 61 medical records per hospital. Based on this sample size for each observation time-point, we are also sufficiently powered to test for within group changes in the control group (post-intervention vs pre-intervention) since within-group comparisons are expected to have a larger power compared to between-group comparisons. Sample size calculations were conducted using the PASS 13 software.

The analysis has been a priori defined to address the research aims. Descriptive statistics will be computed for all variables to ensure data quality, identify patterns of missing and out-of-range values, and evaluate the assumptions of statistical tests. In general, missing data will be evaluated considering both descriptive statistics and possible reasons for non-response. The assumption of missing at random (MAR) [63] is evaluated based on extensive data considerations and discussions with the data collecting personnel on the reasons for nonresponse for the non-medical record data. If the MAR assumption is plausible, multiple imputation methodology will be applied [64]. If there are missing data in more than one variable, multiple imputation through chained equations will be performed [65]. Inclusion of auxiliary variables that are associated with the probability of missingness in the imputation model will be considered in order to make the MAR assumption more plausible. In this case, standard errors will be estimated through nonparametric bootstrap methods in order to avoid the consequences of uncongeniality between the imputation and analysis models on Rubin’s standard error estimator [66, 67]. If there are no variables that make the MAR assumptions plausible, a sensitivity analysis will be performed under various missing not at random scenarios to evaluate the robustness of inference against the violation of the MAR assumption. Remediation of normal distribution assumption violations will be accomplished using methods such as the Box-Cox family transformations, or other methods as appropriate. Assessment of internal consistency reliability of scales will be carried out using the Cronbach’s alpha coefficient. Analysis for each study aim will be performed using the statistical packages SAS or STATA. Any imbalances due to chance will be addressed by including the corresponding variables as covariates in the multivariable regression models for each outcome. Intention-to-treat analysis will be performed in accordance to the pragmatic trial model, in the sense that all participating units will be included in the analysis regardless of their level of adherence to SBIRT.

#### Aim 1

Evaluation of the effect of implementation strategies will be focused on the use of SBIRT. To estimate the effect of implementation (training, toolkit) of SBIRT on clinical processes, we will use multilevel mixed-effects logistic regression models to account for both the hospital unit clustering effects and the potential observation dependence within each phase of the study (i.e., baseline, 6 months, 12 months), while adjusting for variables found to be imbalanced between the study groups. Potential confounders such as organizational and nurse attributes will also be considered for inclusion in the model to avoid any residual confounding effects. Based on these models, both between and within-group effects will be estimated and model-based estimates of the effect size (i.e., odds ratio) will be calculated along with the associated 95% confidence intervals. We will additionally evaluate the intervention effect sustainability in the intervention group by comparing, using the appropriate estimate from the fitted model, the proportion of SBIRT use at 6 months versus the corresponding use at 12 months.

#### Aim 2

Evaluation of the cost of implementation and delivery of SBIRT will be focused on the system perspective. Tailored implementation of SBIRT for local healthcare settings requires appropriate budgeting and resources. Data on both human resources and tangible resource use will be measured during the current study. These data will inform future implementation and budgeting. We will estimate costs of implementation based upon phase of implementation, including the start-up, deployment, and maintenance costs of the adoption of SBIRT. Specific cost categories will collected via the monthly worksheet including personnel (training & education; deployment), site coordinator time spent on implementation, and SBIRT related expenses (e.g., written materials). Costs of SBIRT delivery will be estimated using a random sample of registered nurse’s report of estimated minutes interacting with the patient during the SBIRT process. The cost outcomes will be analyzed using mixed-effects linear regression models to account for the hospital unit clustering.

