## Background

According to the World Health Organization, mental health and substance use disorders will surpass all physical diseases as a major cause of disability worldwide by 2020 [1]. In the United States, the annual total estimated societal cost of substance use disorders is $510.8 billion [2]. The negative outcomes and costs associated with substance use are not exclusive to any specific substance. For example, alcohol use is linked to significant economic and health costs on a global scale [3]. It is often a contributing factor in homicides, suicides, crimes (violent, including homicide, and non-violent), motor vehicle collisions (non-fatal and fatal), and unintentional injuries to the drinker and others in his/her environment [4]. Heavy drinking can lead to a pattern of abuse and/or dependence that is often associated with other harmful behaviors such as cigarette smoking, unsafe sex, and illicit drug use [5]. Even lower levels of drinking, while potentially asymptomatic, are associated with health risks [6].

In addition, despite a steady decline in smoking rates among the general population over the past several decades, tobacco use remains the primary known preventable cause of morbidity and mortality in the United States, resulting in an estimated 480,000 deaths annually from tobacco-attributable diseases [7]. Quitting smoking has a greater impact on cardiovascular risk than changes in blood pressure, weight, physical activity, or lipids [8]. Finally, and of particular relevance to the national public health and medical infrastructure in the United States, the rate of non-medical prescription pain reliever use reported in 2014 by US residents between the ages of 18–25 was 2.8% [9]. Further, between 2004 and 2009, emergency department visits increased 98.4% in the US related to non-medical use of prescription drugs [10]. These data have meaningful implications for the US healthcare system. Over 36.5 million adults are admitted annually to acute care hospitals in the US [11]. In such settings, approximately one-third of adult patients screen positive for high-risk drinking or drug use [12].

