One promising public health response to this problem is screening, brief intervention, and referral to treatment (SBIRT), which is a comprehensive, integrated approach to the delivery of early intervention and referral to treatment services for persons at risk for or with substance use disorders and/or tobacco use and dependence [13]. Rather than a specific, individual service, SBIRT is a patient care framework based on identifying risk via validated screening tools, intervening on that risk in a manner that is clinically appropriate, and referring to specialty treatment when the risk cannot be managed on-site [14]. Data from a large cross-site evaluation from diverse healthcare sites (n = 754,525) indicate that most patients who screen positive are recommended for a brief intervention (BI 68.8%), followed by brief treatment (BT 14.0%) and referral to specialty treatment (RT 17.2%) [15]. However, SBIRT screening in hospital settings tends to identify both a higher frequency of positive screens for alcohol and increased severity level of those screening scores, relative to outpatient primary care, indicating greater likelihood of patients needing referral [16, 17].

The evidence basis for SBIRT is complex and varies considerably by type of substance, activity, and severity of use. Brief interventions (BI) for unhealthy alcohol use (‘misuse’) are supported by a systematic reviews [18–20] as well as the largest SBIRT evaluation study to date [15]. Alcohol BIs have also demonstrated efficacy for underage drinkers in the ED [21]. However, alcohol BI does not appear to be efficacious for very heavy or dependent users [22]. Further, a recent meta-analysis found no evidence that BI, naturally results in engagement with alcohol-related care [23], though other researchers have disputed this claim [24]. Few SBIRT studies focus specifically on outcomes from referral to treatment (RT) for alcohol [25], sometimes due to difficulty disentangling the type of service provided [26], though the cross-site evaluation from SAMHSA’s SBIRT initiative reported a moderate/large effect for RT [15]. Due to this deficit in the literature, one research team recently conducted a proof-of-concept study for their alcohol RT, yielding promising results for patient engagement with treatment post-SBIRT [27].

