### Study design and sample

A phased cluster randomized mixed methods design will be used for this study. Each hospital within the healthcare system is eligible to participate, and the chief nursing officer of each hospital (N = 14) submitted a letter of support for the study. One medical surgical unit within each hospital will be selected by the nurse executive to participate. This selection will be based on the nurse executive’s assessment of the nursing unit capacity to participate in the study and implement a change in practice.

A computer-generated allocation based on a stratified random sampling approach using STATA will be used to randomize hospitals into an intervention or wait-list usual care control group. Prior to randomization, hospitals will be stratified by type (academic health center, community hospital, or critical access hospital). Allocation to the intervention or wait-list usual care control groups will be based on cluster, and participants will be notified of their cluster allocation. Participants in the control group will provide the usual care that is standard for that facility, and then the site coordinators will receive the intervention 6 months after participants in the intervention group (Table 2).

**Table 2 Tab2:** Study design

	Collect pre-data	Intervention		Collect 6-month data	Collect 12-month data
Group 1 (Intervention Group)	0_1_	×		0_2_	0_3_
Group 2 (Wait-List Usual Care Control Group)	0_1_		× (6 months after Group 1)	0_2_	0_3_

All hospitals will receive the intervention. Group 1 (n = 7) hospitals will participate in the implementation intervention first, with Group 2 (n = 7) following 6 months later. Using this phased approach allows for comparisons between a control and intervention group, as well as within hospital changes longitudinally, and ensures there are no ethical concerns related to withholding the SBIRT implementation.

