The consequences of SBIRT implementation include the delivery of SBIRT components and the costs of implementation. Delivery of SBIRT components will be measured by the documentation of screening, brief intervention, and referral to treatment for alcohol, drugs, and tobacco, individually and combined. These data will be based on the Joint Commission Quality Measures for alcohol, drug, and tobacco use [60]. The components of SBIRT will be documented in the medical record by healthcare providers who complete the screening, brief intervention, and referral to treatment. All hospitals use the same electronic medical record system. Sixty-one medical records at each site will be randomly selected through automated processes. Inclusion criteria are adult (≥ 18) patients admitted and discharged from units selected for participation in this study within data abstraction periods (baseline, 6 months and 12 months). De-identified data will be abstracted using an electronic data abstraction report. Automated data abstraction will be validated via comparison of electronic and manual data abstraction in a sub-sample of records at each hospital. If required, the site coordinators will conduct the medical record review manually. We will collect data regarding the number of patients screened for alcohol, tobacco, and drugs using a validated tool, and the percentage of patients who screened positive for each substance and then received a brief intervention and/or referral to treatment. The costs of implementation will be assessed using the monthly worksheets completed by the site coordinators and the SBIRT use reports. Data regarding care delivery and costs of implementation will be assessed. At the completion of the study, site coordinators will complete a semi-structured interview to describe their experiences as well as barriers and facilitators of implementation.

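### The 80% power for a 16-point difference reproduces only for documented screening; it is not supported for brief intervention and referral, which rest on fewer records

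*Protocol article*

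**What the plan says.** The Statistical analysis section sets out "to achieve an 80% power at an alpha level of 0.05 to address the quantitative aims of the study". It then gives the inputs: "Sample size calculations were based on an intracluster correlation of 0.03"; "For the between-group comparisons regarding the binary outcomes of Aim 1, detecting an absolute difference in a proportion between the two groups of 16" per cent; and, "using a Z-statistic that accounts for the intracluster correlation, requires 61 medical records per hospital". Study design and sample fixes the clusters: "Group 1 (n = 7) hospitals will participate in the implementation intervention first, with Group 2 (n = 7) following 6 months later". No control proportion is stated, and nothing limits the claim to one component of SBIRT.

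Data sources draws the 61 records per site from all adult patients admitted to and discharged from the study unit. It names screening, BI and RT as the components to be measured, for each substance and combined. Screening is a count of patients screened. BI and RT are read as "the percentage of patients who screened positive for each substance and then received a brief intervention and/or referral to treatment".

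The Background supplies the only shares in the document. In acute care hospitals, "approximately one-third of adult patients screen positive for high-risk drinking or drug use". In a large cross-site evaluation, 68.8% of patients with a positive screen were recommended for BI, followed by "brief treatment (BT 14.0%) and referral to specialty treatment (RT 17.2" per cent). The Background adds that hospital patients are likelier than primary care patients to need referral. The Discussion allows that nothing beyond the initial screening may be documented at baseline.

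**The concern.** One sample size and one effect size are declared sufficient for outcomes with different denominators. Every sampled record contributes to documented screening. Only records with a positive screen contribute to BI and RT, and the calculation does not reduce the 61 accordingly.

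The Abstract makes documentation of SBIRT delivery the primary endpoint, and BI and RT are two of its three components. A reader who trusts the power statement could take a null result for BI or RT as failed implementation, when the sample may have had little chance of showing a 16-point change.

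**Working it through.** **Inputs.** From the article: two-group comparison, alpha 0.05, power 80%, intracluster correlation (ICC) 0.03, 7 units per arm, 61 records per unit per time point, difference 16 points; one-third screen positive (alcohol or drugs); 68.8% and 17.2% of positives recommended for BI and RT. Assumed: two-sided test, equal cluster sizes, ICC 0.03 also within subsets, and that the cited shares apply to these units.

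**Formulas.** With m records per unit in the denominator:

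- design effect DE = 1 + (m − 1) × 0.03
- effective n per arm = 7m / DE
- power = Φ{[d√n − 1.96√(2p̄(1 − p̄))] / √(p₁(1 − p₁) + p₂(1 − p₂))}, the pooled-variance Z-test, with d = 0.16 and p̄ the mean of p₁ and p₂

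**Reproducing the plan's figure.** m = 61: DE = 1 + 60 × 0.03 = 2.80; n = 427 / 2.80 = 152.5. At 42% vs 58%: [0.16 × 12.35 − 1.96 × 0.7071] / 0.698 = 0.845, so power is 80.1%. The smallest m that reaches 80% is exactly 61. Other proportions need fewer records (52 at 30% vs 46%, 21 at 10% vs 26%). So 61 is the worst-case-variance figure with every record counted.

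**Same proportions (42% vs 58%), smaller denominators.**

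| Denominator | m | DE | Effective n per arm | Power |
|---|---|---|---|---|
| All records | 61 | 2.80 | 152.5 | 80.1% |
| Half positive (assumed) | 30.5 | 1.885 | 113.3 | 67.5% |
| One-third positive (Background) | 20.33 | 1.58 | 90.1 | 57.5% |
| Single substance, 20% positive (assumed) | 12.2 | 1.336 | 63.9 | 44% |
| Single substance, 10% positive (assumed) | 6.1 | 1.153 | 37.0 | 28% |

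With one-third positive, the difference detectable with 80% power, centred on 50%, is about 21 points. The 20 records per unit already suppose that every patient is screened.

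**Dependence on the control rate.** Among one-third positives, power for 16 points is 60% at a control rate of 30%, 67% at 20%, 80% at 10%, 90% at 5% and 95% at 2%. The 80% level is met up to a control rate of about 10%.

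**RT for alcohol or drugs over all records.** Ceiling = 1/3 × 17.2% = 5.7%. Doubling the referral share, because hospital patients are likelier to need referral, gives 1/3 × 34.4% = 11.5%. A 16-point difference exceeds both.

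**RT among patients recommended for referral (assumed denominator).** m = 61 × 1/3 × 0.172 = 3.5; DE = 1.075; n = 22.8. Power is 19% at 42% vs 58% and 47% at 1% vs 17%. With the referral share doubled, m = 7.0, n = 41.5, and power at 1% vs 17% is about 73%.

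**The case against.** A reader might infer that BI and RT cannot have 80% power on the article's own figures, whichever denominator is used. The documents do not support that.

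- **BI among positives.** The 57.5% uses the least favourable variance. The Discussion foresees little documentation at baseline, and the Background says brief interventions are often not conducted, so a low control rate is plausible. At 10% or below, 80% is reached.
- **BI over all records.** The ceiling is 1/3 × 68.8% = 22.9%. A change from 5% to 21% fits under it and has about 99% power with 61 records.
- **RT among all positives.** With a 17.2% ceiling, a 16-point rise needs a control rate of about 1% and nearly every indicated referral made. That is demanding, but not impossible.
- **The shares.** The one-third covers alcohol or drugs only, and no tobacco prevalence is given. The 17.2% is for specialty treatment across diverse sites, so the 5.7% ceiling does not bind tobacco RT (which can be a quit line referral) or combined RT. Nothing in the article restricts RT to the 3.5 patients per unit recommended for referral.

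All of this stands, and it rules out the word cannot. It does not rescue the statement as written, which assumes neither a low control rate nor a reduced denominator.

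A second stronger reading is that few positives will be found in control units, since the Background says validated tools are rarely used under usual care. That would shrink the control denominator further, but the article gives no identification rates, so no power figure can be attached.

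It may also be said that a condensed article leaves power by component to the full protocol. That would excuse silence. Here the article makes an affirmative claim covering all the binary outcomes.

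**Conclusion.** The power statement is wrong as written for BI and RT. It reproduces for documented screening, where all 61 records count.

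For BI and RT among screen-positives, the proportions behind the 61 give 57.5% power at the cited one-third share. This rises to 67.5% if half are positive and falls to 44% or 28% for a single substance at 20% or 10% positive. Power of 80% is regained at one-third positive only with a control rate of about 10% or lower, which the Discussion makes possible but the calculation does not assume.

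The strongest part concerns alcohol or drug RT. Over all records, 16 points is above the ceiling of 5.7% (11.5% with the referral share doubled). Among patients recommended for referral, power is 19% to 47%. The latter rests on a denominator the article does not define.

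The conclusion is that the claim is unsupported for BI and RT, not that these outcomes are necessarily underpowered. It depends on the assumptions listed with the inputs, above all that the cited shares carry over to these units.

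**What to change.** Confine the 80% and 16-point statement to documented screening, with all 61 records as the denominator. For BI and for RT, add the denominator, the expected number of positive records per unit, the assumed control proportion, and the resulting power or detectable difference, for combined and single substances where both will be reported. State any tobacco prevalence used. Report BI and RT with estimates and confidence intervals, so that a null result is not read as failed implementation.

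This is a wording change. It needs no extra records and no change to the endpoint hierarchy; BI and RT can stay where they are. The cost is a less favourable stated power for these two components.

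### The stated 80% power rests on a normal (Z) reference for 7 v 7 units; at the near-50% proportions that 61 records imply, power on 12 degrees of freedom is about 74%

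*Protocol article*

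**What the plan says.** In the protocol article, the Statistical analysis section sets out to find the number of records per hospital "to achieve an 80% power at an alpha level of 0.05". Its inputs are a 16-point absolute difference and one ICC: "Sample size calculations were based on an intracluster correlation of 0.03". The result is that detecting this difference "with an at least 80% power, using a Z-statistic that accounts for the intracluster correlation, requires 61 medical records per hospital". On sensitivity to the ICC it says only this: "In case intracluster correlation is lower than 0.03, our statistical tests provide an even larger statistical power".

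Study design and sample gives the number of randomised units: "Group 1 (n = 7) hospitals will participate in the implementation intervention first, with Group 2 (n = 7) following 6 months later". There is one unit per hospital, and randomisation is stratified by three hospital types.

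For Aim 1 the article says "we will use multilevel mixed-effects logistic regression models to account for both the hospital unit clustering effects and the potential observation dependence", with odds ratios and 95% confidence intervals. It does not say whether the model's tests use a normal or a t reference. It gives no control-group proportion.

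**The concern.** Allowing for the ICC makes the standard error larger. It does not alter the reference distribution. A Z-statistic treats the between-unit variance as known, but here it is estimated from 14 units: 14 - 2 = 12 degrees of freedom, or 14 - 2 - 2 = 10 once the three strata are fitted. The two-sided 5% critical value is then 2.179 or 2.228 rather than 1.960. With so few units this is enough to bring the power below the stated minimum.

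The ICC sentence is true but covers only the favourable direction. A reader is not told how fast power falls if the ICC exceeds 0.03.

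At stake is whether the trial has the power it claims for its main between-group comparison, and whether the final tests and intervals will reflect 14 units.

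**Working it through.** **Inputs from the protocol article.** Seven units per group; m = 61 records per unit per time point; ICC = 0.03; difference 0.16; alpha 0.05; power at least 80%.

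**Assumptions.** Two-sided alpha, since the article does not say (one-sided alpha would give about 88% at 42% v 58%). Proportions of 42% v 58%, with a range below. One time point.

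**1. Reproducing the plan's figure.**
- Records per group without clustering, pooled Z formula: [1.960 x sqrt(2 x 0.25) + 0.8416 x sqrt(2 x 0.2436)]^2 / 0.16^2 = 152.1.
- Records per unit with clustering: 152.1 x (1 - 0.03) / (7 - 152.1 x 0.03) = 60.6, that is 61.
- At 20% v 36% the same formula gives about 36 records per unit, so the figure of 61 points to planning near 50%.

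**2. Power with Z.**
- Design effect: 1 + 60 x 0.03 = 2.8.
- Effective records per group: 7 x 61 / 2.8 = 152.5.
- Standard error: sqrt(2 x 0.2436 / 152.5) = 0.0565.
- Standardised difference: 0.16 / 0.0565 = 2.83.
- Power: Phi(2.83 - 1.96) = 80.8% (80.1% with the pooled variance under the null). The stated figure is reproduced.

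**3. Power with t.** Same standard error, noncentral t with noncentrality 2.83:

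| Reference | Critical value | Power at 16 points | Difference detectable at 80% | Records per unit for 80% at 16 points |
|---|---|---|---|---|
| Z | 1.960 | 80.8% | about 16 points | 61 |
| t, 12 df | 2.179 | 73.9% | 17.2 points | 103 |
| t, 10 df | 2.228 | 72.3% | 17.5 points | 121 |

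A simulated t test on unit proportions at 42% v 58% gave 73.1%, in agreement with the 12 df row.

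**4. Dependence on the unstated proportions** (ICC 0.03, 61 records, 16 points):

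| Proportions | Z | t, 12 df | t, 10 df |
|---|---|---|---|
| 42% v 58% | 80.8% | 73.9% | 72.3% |
| 34% v 50% | 81.8% | 75.0% | 73.4% |
| 30% v 46% | 83.1% | 76.4% | 74.9% |
| 24% v 40% | 86.0% | 79.7% | 78.2% |
| 20% v 36% | 88.5% | 82.7% | 81.3% |
| 10% v 26% | 96.1% | 92.6% | 91.7% |

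**5. A higher ICC** (illustrative values, not from the protocol; 42% v 58%, 12 df):
- ICC 0.05: design effect 1 + 60 x 0.05 = 4.0, effective records 106.75 per group, power 59%.
- ICC 0.10: design effect 1 + 60 x 0.10 = 7.0, effective records 61 per group, power 38%.

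**6. Type I error if the mixed model were read with an uncorrected Wald z test.**
- A 1.96 cut-off on a statistic that follows t with 12 df rejects a true null 7.4% of the time.
- Simulated random-intercept logistic models at one time point (14 units, 61 records, ICC 0.03, 4,000 trials per setting) gave 8.4%, 8.8% and 8.8% at proportions of 50%, 30% and 10%. With a t reference on 12 df, the same models gave 5.6%, 6.3% and 6.0%.
- In three-period models the six-month between-group contrast gave 8.4% to 11.1%. Two of those four settings had only about 320 trials each, with a Monte Carlo error of about 1.5 points.

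**The case against.** **The arithmetic is not wrong.** The article names its test, its ICC and its effect size, and 61 follows from them. This stands. The fault is the choice of reference distribution for 14 units.

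**The 74% depends on a proportion that the protocol does not give.** This stands too. The Discussion allows that nothing beyond initial screening may be documented at baseline, which points to low rates for brief intervention and referral. At such rates the stated minimum can hold even with t. But 61 records correspond to planning near 50%, and there it does not hold.

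**The analysis uses baseline data as well.** With unit-level adjustment for baseline and 11 degrees of freedom, power at 42% v 58% would be 76.1%, 80.0% or 85.6% if the between-period correlation of the unit effects were 0.4, 0.6 or 0.8. Those correlations are assumptions, and this is not the calculation that the article states. It may be offered as a supplement, with its assumption declared.

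**The mixed model may do better than a t test on unit proportions.** In simulation at 42% v 58%, the mixed model with a t reference on 12 df had 77.6% power, still below 80% and with a type I error of about 6%. With Wald z it had 83%, but with the inflated error shown above.

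**A stronger reading.** A reader might infer that the planned test rejects a true null about twice as often as it should. The article does not support that. Its Z-statistic belongs to the sample-size calculation. The Aim 1 text names no reference distribution, and the analysis plan, which was not available for this review, may settle it. The inflation applies only to an uncorrected Wald z test.

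**Conclusion.** The power statement needs correction. At the proportions that 61 records imply, the claimed minimum of 80% is about 74% on 12 degrees of freedom and 72% on 10: a shortfall of roughly 6 to 8 percentage points, or 1.2 to 1.5 points in the detectable difference. This assumes a two-sided test, ICC 0.03, one time point without baseline adjustment, and proportions near 50%. It is not an unconditional 74%: the lower the documentation rates, the smaller the shortfall, and on 12 degrees of freedom it is gone at about 24% v 40%.

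The one-sided ICC remark is true but incomplete. The type I error figures are a reason to fix the reference distribution in advance. They do not show that the trial plans an invalid test.

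**What to change.** 1. State the proportions behind the 61 records and whether alpha is two-sided.
2. Restate the result with t degrees of freedom for 14 units. If planning was at 42% v 58%: about 74% power for 16 points on 12 df (72% on 10), or 80% for about 17.2 points (17.5 on 10). If lower rates were assumed, give the power for those.
3. Beside the remark on a lower ICC, give the power for higher values, for example 0.05 and 0.10, labelled as illustrative.
4. Keep the mixed-effects logistic model, and specify that its between-group tests and 95% confidence intervals use t with between-unit degrees of freedom. Since this reference still gave 5.6% to 6.3% in simulation, add a permutation test as a check. If each stratum (4, 4 and 6 hospitals) is split equally, there are 6 x 6 x 20 = 720 allocations.

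This needs no further hospitals or records, only changes to the wording and the specified analysis. The price is a slightly lower stated power and slightly wider intervals.

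### Covariates are to be chosen by observed imbalance among 14 units, a rule that passes over the stratification factor, hospital type, and no model commits to including it

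*Protocol article*

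**What the plan says.** Under Study design and sample, the protocol article states: "Prior to randomization, hospitals will be stratified by type (academic health center, community hospital, or critical access hospital"). Study subjects and Table 1 give four academic, four community and six critical access hospitals. Each contributes one unit, and seven hospitals go to each group.

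The Statistical analysis section sets a covariate rule for all outcomes: "Any imbalances due to chance will be addressed by including the corresponding variables as covariates in the multivariable regression models for each outcome". The Aim 1 paragraph repeats it for the mixed-effects logistic model, to be fitted "while adjusting for variables found to be imbalanced between the study groups". The next sentence opens a second route: "Potential confounders such as organizational and nurse attributes will also be considered for inclusion in the model". No sentence names hospital type as a term in any model. The same section describes the analysis as defined in advance.

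**The concern.** Two things are wrong with the rule as stated.

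First, it settles the model after the data are seen. With 14 units, some unit-level characteristics will look imbalanced by chance. Which ones do says nothing about whether they predict the outcome. The second route adds a further choice with no stated criterion. A covariate set reached in this way is not defined in advance.

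Second, the rule looks for imbalance, and stratification exists to remove it. If each stratum is split evenly, hospital type cannot be found imbalanced. The factor judged important enough to stratify on is then the one that the rule cannot pick up. After stratified randomization, leaving out a prognostic stratum factor keeps its variance in the residual, although the design has already removed it from the treatment contrast. The reported standard error is then too large for the comparison of levels between groups.

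**Working it through.** **Inputs from the protocol article.** 7 v 7 hospitals; strata 4/4/6; 61 records per hospital per time point; "Sample size calculations were based on an intracluster correlation of 0.03"; the target is "detecting an absolute difference in a proportion between the two groups of 16" percent, and the sample size is set "to achieve an 80% power at an alpha level of 0.05".

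**Assumptions.** Two-sided test; proportions near 0.5 (the base proportion is not stated); each stratum halved exactly (2/2, 2/2, 3/3); and *R*, the share of between-unit variance due to hospital type, for which the protocol gives no figure. *R* is therefore shown over a range.

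**The plan's own figure.** For 0.42 v 0.58, a pooled two-proportion test needs n = 153 effective records per arm. With design effect 1 + (m − 1) × 0.03 and 7 hospitals, m = n(1 − 0.03)/(7 − 0.03n) = 148.41/2.41 = 61.6. For 0.40 v 0.56, n = 152 and m = 147.44/2.44 = 60.4. At m = 61 the design effect is 2.8, the effective size is 7 × 61/2.8 = 152.5 per arm, and power is 0.80. The stated 61 is reproduced. This formula takes no credit for stratification.

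**Standard error with and without type.** On the proportion scale at p = 0.5:
- between-unit variance: 0.03 × 0.25 = 0.0075
- sampling variance of a unit mean: 0.97 × 0.25/61 = 0.003975
- residual variance once type is removed: V = (1 − R) × 0.0075 + 0.003975
- true SE of the group difference: √(2V/7)
- SE reported without type: about √{(2/7)[V + (14/12) × R × 0.0075]}

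At R = 0.5, V = 0.007725. The true SE is 0.047 and the reported SE is √(0.0121 × 2/7) = 0.059, about 25% too large.

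**Simulation of the 6-month between-group contrast.** 40,000 trials of unit means, a normal approximation to the mixed logistic model; t reference with 12 df without type and 10 df with it.

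| R (assumed) | Type I error, without → with type | Power, without → with type |
|---|---|---|
| 0 | 5.0% → 5.1% | 73% → 71% |
| 0.25 | 3.3% → 5.1% | 74% → 79% |
| 0.50 | 1.6% → 5.0% | 74% → 87% |
| 0.75 | 0.6% → 5.1% | 75% → 94% |
| 0.90 | 0.2% → 5.2% | 77% → 97% |

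Separate runs of 20,000 trials agree within about a point (at R = 0.25, type I error 3.2% and power 73% → 78–79%). Interval coverage at R = 0.5 is 98.4% without type and about 95% with it. The 73% at R = 0, against the planned 80%, comes from using a t rather than a normal reference, not from omitting type.

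**Change-from-baseline contrast.** This assumes that 80% of the remaining between-unit variance is stable over time. Type I error is about 5% with or without type. Power without → with type is 75% → 73% at R = 0, 81% → 79% at R = 0.5 and 86% → 84% at R = 0.9. Stable differences between types cancel, so omission does no harm.

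**Exposure to chance imbalance.** Suppose k independent, irrelevant unit-level candidates are screened at p < 0.10 (a threshold assumed here; the protocol gives none). The chance that at least one is flagged is 1 − 0.90^k: 41% for k = 5 and 65% for k = 10.

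**The case against.** The strongest reply is that hospital type is not shut out. It is plausibly an organizational attribute, and the Aim 1 paragraph allows those to be considered. That stands, so a reader who infers that type can never enter the model goes too far. The imbalance rule cannot select it, but the second route could. Considering a variable is still not committing to it. The even split within strata is also inferred rather than stated.

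The harm is also conditional. Type must be left out, it must predict the outcome, and the contrast must be of 6-month levels. The protocol describes a multilevel model over three phases and does not say which contrast is primary. However, the sample size rests on a between-group comparison, "using a Z-statistic that accounts for the intracluster correlation, requires 61 medical records per hospital", so the exposed contrast is the one on which the trial was powered.

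The wide bed range does not show that type is a strong predictor. Table 1 gives beds per hospital, not per unit, and the academic stratum alone runs from 38 to 858. All sites share one health system and one record system. The share of variance due to type is therefore open.

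A reader might also infer that the plan misuses the baseline records and should adjust for each unit's baseline proportion. The documents do not carry that. They specify neither a change score nor a post-only analysis. The variance penalty of a change score over baseline adjustment depends on an assumed autocorrelation (51% at 0.5, 31% at 0.8). The Discussion also warns that baseline records may hold nothing beyond initial screening, so baseline brief intervention and referral may be near zero and carry little information.

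Finally, a full covariate list is commonly left to an analysis plan. That is so, but here the article states a selection rule, twice, and the rule is the problem.

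**Conclusion.** The point holds in limited form. The stated rule is data-driven and passes over the stratification factor, and nothing else in the article commits hospital type to a model.

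For a 6-month between-group comparison that omits type, power forgone is about 5 points if type explains 25% of between-unit variance and about 13 points if it explains 50%. Type I error is about 3.2% and 1.6% respectively. Both shares are assumptions. If type explains nothing, there is no harm.

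Two stronger readings are not supported. One is that the planned 80% power is cut: the sample-size formula never counted on stratification, and at the planned ICC, power without type (74–77%) is no lower when type matters than when it does not (73%). What is lost is attainable precision. The other is that omitting type produces false positives: it widens intervals and lowers type I error. The figures concern Aim 1 under a t reference and a linear approximation. No size was computed for the Aim 2 cost models, to which the same rule applies.

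**What to change.** In the general Statistical analysis text and the Aim 1 paragraph, replace the imbalance rule with hospital type (three levels) as a fixed covariate, and say the same for the Aim 2 models. Name any other covariate in advance on prognostic grounds. Report adjustment for variables found imbalanced as sensitivity analysis only.

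State a small-sample reference distribution alongside this. With a normal reference, the simulated type I error with type included was about 8% (7.8% at R = 0.5).

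The cost is a change of wording, since hospital type is already known for every site. It uses 2 of about 12 between-unit degrees of freedom, or 1–2 points of power if type turns out not to predict the outcome.
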